#### Household survey

A total of 412 children under 10 years of age in 4 clusters per arm will be sampled to detect a minimum of 10% increase in malaria testing rate (from 10 to 20% in the intervention arm) and 10% difference in testing rate between the intervention arm (20%) and control arm (10%) after 12 months of deployment of interventions with 80% power and 5% significance level. This computation is based on the standard formula for randomized controlled trials described by Hemming and colleagues [23] and the application of a variance inflation factor (VIF) of 2.92 (based on an intracluster coefficient of 0.02 and an average cluster size of 97).

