## Methods/design

### Study design

The proposed interventions will be evaluated using a two-arm (intervention and control), cluster randomized trial across 8 rural clusters (4 clusters per arm), in two adjacent districts of Ghana. The method of Wiseman et al. will be used in this study with some modifications [21]. Wiseman et al. used a three-arm stratified cluster randomized trial to evaluate the effectiveness and cost-effectiveness of two interventions designed to support the roll-out of mRDTs and improve the rational use of ACTs. They focused in part on private medicine retail outlets (known as OTCMS in Ghana), who are the focus of this study. Wiseman et al. looked at the effectiveness of individual interventions, but this study will evaluate the combined effectiveness of different interventions.

A cluster is defined as a geographical community which contains at least one OTCMS, and this will be the unit of randomization within each study arm.

The intervention arm has 8 clusters, and out of these, 4 will be randomly selected using a computer-generated list. The control arm has 4 clusters, and all these will be included in the study (Fig. 1). An urban sub-district (Begoro) in the intervention district will act as a buffer between the two arms. This method is adopted to reduce contamination (that is, filtering of information across the two arms) to the barest minimum. The selected four clusters per study arm will yield a total of 8 OTCMS in the intervention arm and 5 OTCMS in the control arm.

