#### Preparatory phase

The preparatory phase will involve scheduled meetings with stakeholders including the district and regional health directorates, the National Malaria Control Programme (NMCP), relevant non-governmental organizations such as Strengthening Health Outcomes through the Private Sector (SHOPS), and OTCMS and traditional leaders in the selected communities. These engagements will create the required awareness and subsequently obtain permissions and support in the conduct of the study.

As part of the preparatory phase, houses in the selected clusters will be mapped, and lists of households with children under 10 years old will be generated with corresponding GPS coordinates.

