#### End-line household survey

Children less than 10 years old in both intervention and control arms

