### Outcomes

#### Primary outcome

The primary outcome is the proportion of children under 10 years with fever or suspected to have malaria visiting OTCMS and tested before treatment.

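### The 412 children are defined by age alone, but the primary outcome counts only febrile or suspected-malaria children who visited an OTCMS, so the stated 80% power holds only if every sampled child is eligible

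*Protocol article*

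**What the plan says.** All references are to the protocol article.

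- **Sample size estimation, Household survey:** "A total of 412 children under 10 years of age in 4 clusters per arm will be sampled", to detect testing rates of 20% against 10% "with 80% power and 5% significance level". Clustering enters through a "variance inflation factor (VIF) of 2.92 (based on an intracluster coefficient of 0.02 and an average cluster size of 97").
- **Inclusion criteria, End-line household survey:** "Children less than 10 years old in both intervention and control arms". The exclusion criterion is also by age only, and the baseline criterion has the same form for the intervention arm.
- **Preparatory phase:** houses are mapped and "lists of households with children under 10 years old will be generated".
- **Outcomes, Primary outcome:** the proportion of "children under 10 years with fever or suspected to have malaria visiting OTCMS and tested before treatment".
- **Evaluation phase, Household survey:** the primary outcome comes from the end-line household survey, which follows the baseline survey. The baseline survey asks about fever and OTCMS visits in the preceding month.

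No section gives the proportion of children with fever in a month, the proportion of those taken to an OTCMS, or an inflation of the sample for either.

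**The concern.** The number being powered and the number being analysed refer to different children. A child with no fever in the past month, or with fever but treated elsewhere, meets the sampling criterion and counts toward 412 but cannot enter the primary outcome. If the field team samples by the stated criterion, the 10% versus 20% comparison rests on fewer children than the calculation assumes, and the stated power does not apply to it. This concerns the only primary outcome. With four clusters per arm, it also affects how much information each cluster contributes to the planned random-effects logistic model.

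**Working it through.** **Inputs from the protocol.** Control rate 0.10, intervention rate 0.20, difference 0.10; power 80%; significance level 5% (sidedness is not stated, two-sided taken); ICC 0.02; cluster size 97; 4 clusters per arm; 412 children.

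**Input not in the protocol.** The share *f* of sampled children who had fever or suspected malaria in the past month and visited an OTCMS. It is assumed here at 50, 30, 20 and 10%, with 100% as the reference.

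**Step 1: reproduce the plan's figure.**
- VIF = 1 + (97 − 1) × 0.02 = 2.92, as stated.
- Using the control variance in both arms: n = 2 × 0.10 × 0.90 × (1.96 + 0.8416)² / 0.10² = 0.18 × 7.849 / 0.01 = 141.28.
- 141.28 × 2.92 = 412.5.

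So 412 is a per-arm number, although the text calls it a total. Effect size, power, significance level and VIF account for all of it. Nothing is left for fever prevalence, OTCMS attendance or non-response.

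**Step 2: analysable children and power by share.** With 412 sampled per arm, 412/4 = 103 per cluster, so:
- eligible per cluster m = 103*f*
- design effect = 1 + (m − 1) × 0.02
- effective n per arm = 4m / design effect
- power, plan's control variance = Φ(0.10/√(0.18/effective n) − 1.96)
- power, usual two-arm variance (0.09 + 0.16 = 0.25) = Φ(0.10/√(0.25/effective n) − 1.96)

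| Share *f* | Eligible per arm | m | Design effect | Effective n per arm | Power, plan's variance | Power, two-arm variance |
|---|---|---|---|---|---|---|
| 100% | 412 | 103 | 3.04 | 135.5 | 78% | 64% |
| 50% | 206 | 51.5 | 2.01 | 102.5 | 67% | 53% |
| 30% | 124 | 30.9 | 1.60 | 77.3 | 55% | 42% |
| 20% | 82 | 20.6 | 1.39 | 59.2 | 44% | 34% |
| 10% | 41 | 10.3 | 1.19 | 34.7 | 28% | 22% |

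The first row is 78% rather than 80% because 103 children per cluster give a design effect of 3.04, not 2.92. The difference between the last two columns comes from applying the control variance to both arms. That is a separate issue, and the effect of the present point is read down a column, not across.

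The loss is less than proportional to the lost children because the design effect shrinks with cluster size; the table already credits this.

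**Step 3: if 412 means both arms together.** There are then 206 per arm at a 100% share, so power starts at the 50% row (67% or 53%). A 20% share then leaves 41 per arm, which is the 10% row (28% or 22%).

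**Step 4: screening needed for 412 eligible per arm.** 412/*f* = 824 (50%), 1,374 (30%), 2,060 (20%), 4,120 (10%) children per arm.

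**The case against.** The strongest reply is that 412 was always meant to count analysable children. The sample size is framed on the malaria testing rate, and the baseline survey section defines that rate among children who visited an OTCMS for malaria treatment in the past month. The household list settles nothing either way: fever in the month before a later survey cannot be known at mapping, so any frame must list all households with young children. The inclusion criteria are one-line summaries, and an article may leave screening details to the full protocol.

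This reading is possible, and the point about the household list stands. But the sample-size sentence and the end-line criterion both name children by age and nothing else. Elsewhere the authors name the condition where they apply it: the mRDT quality survey counts suspected uncomplicated cases visiting OTCMS, adds 20% for non-response, and restricts eligibility to suspected cases. If eligible visitors were meant, the wording still has to change.

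Two further objections also stand. The size of the loss cannot be derived from the documents, because the eligible share is not given. And a reader might infer that the survey will stop at 412 children, leave a handful per cluster and lose most of its power. The documents contain no such stopping rule. Even the assumed shares of 10 to 50% leave about 10 to 52 children per cluster, and at 50% the loss is about 11 percentage points on either variance.

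**Conclusion.** The point holds as a mismatch between the unit counted in the sample size and the unit in the primary outcome. As written, 80% power is obtained only if all 412 children per arm had fever or suspected malaria and visited an OTCMS within the recall month.

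The loss depends on an assumed share. For shares from 50% down to 10%, power falls from 78% to between 67% and 28% by the plan's own formula, or from 64% to between 53% and 22% with the two-arm variance. These figures assume 412 per arm, equal clusters, ICC 0.02, a two-sided 5% test and a normal approximation. It would be wrong to set the two-arm figures against the stated 80% and attribute the whole gap to this mismatch, since part of it is already present when every child is eligible.

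**What to change.** In the household-survey sample size and the end-line inclusion criterion, define the analysis unit as a child under 10 with fever or suspected malaria in the past month who visited an OTCMS. State that the 412 is per arm and counts those children, found by working through the existing household list in random order with a short screen on fever and OTCMS visit.

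If 412 eligible children per arm cannot be reached in the four communities, keep the planned survey and state the expected eligible number per arm, the share it assumes and the power it gives.

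The rewording costs little. The screening may not: it means 824 children per arm at a 50% share and 2,060 at 20%, and the article gives no community populations to show whether that is feasible. The fallback costs only a less favourable stated power. Recruitment began in September 2019 according to Trial status, so the baseline criterion should be changed only if that survey has not yet been done.

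### The household-survey sample of 412 does not follow from its stated inputs: they require 573 to 581 children per arm, and 412 per arm gives about 64 to 66% power, not 80%

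*Protocol article*

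**What the plan says.** The protocol article sizes the household survey in one paragraph under Sample size estimation: "A total of 412 children under 10 years of age in 4 clusters per arm will be sampled". The target is a testing rate of 20% against 10%. It is given both as a rise within the intervention arm and as a difference between arms, "after 12 months of deployment of interventions with 80% power and 5% significance level". The method is the "standard formula for randomized controlled trials described by Hemming and colleagues", with "the application of a variance inflation factor (VIF) of 2.92 (based on an intracluster coefficient of 0.02 and an average cluster size of 97".

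The paragraph does not state whether the test is one- or two-sided, and it does not show the size before inflation.

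Two other places matter. The Evaluation phase section says the end-line household survey measures the primary outcome, so this is the sizing of the primary comparison. The Study design section says the control arm has four clusters in all and that all four are used.

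**The concern.** The rates, power, significance level, intracluster correlation, cluster size, inflation factor and sample size are all printed, so the result can be checked directly. They do not agree with one another. This is not a detail left to an analysis plan, because no analysis plan can make 412 follow from these inputs.

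The stated power sets how a null result will be read. At 80% power, a true 10-point effect would be missed one time in five. If 412 is per arm, it would be missed about one time in three. If 412 is the total, it would be missed about one time in two or more often. A reader who trusts the printed 80% could take a null result as stronger evidence against a 10-point effect than the design can supply.

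**Working it through.** **Inputs** (household-survey sample size paragraph unless noted): p1 = 0.10, p2 = 0.20, power 80%, significance level 5%, intracluster correlation 0.02, average cluster size 97, variance inflation factor (VIF) 2.92, 4 clusters per arm (also in Study design), sample 412. A two-sided test is assumed, so (1.96 + 0.8416)^2 = 7.849.

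**1. The inflation factor.** 1 + (97 - 1) x 0.02 = 2.92. This agrees with the article.

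**2. The required size.**
- Separate variances: 7.849 x (0.10 x 0.90 + 0.20 x 0.80) / 0.10^2 = 7.849 x 0.25 / 0.01 = 196.2 per arm.
- Pooled variance under the null: 199 per arm.
- After inflation: 196.2 x 2.92 = 573, and 199 x 2.92 = 581 per arm. That is about 1,146 to 1,162 in all, or about 6 clusters of 97 per arm (573/97 = 5.9).

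**3. Attempts to reproduce 412 (per arm, after VIF 2.92).**

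| Variant | Per arm |
|---|---|
| Separate variances | 573 |
| Pooled | 581 |
| Continuity-corrected | 639 |
| Arcsine | 569 |
| One-sided (separate / pooled) | 451 / 458 |
| Control-arm variance in both arms | 412.5 |

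Only the last one matches: 2 x 0.09 x 7.849 / 0.01 = 141.3, and 141.3 x 2.92 = 412.5. It uses 0.10 x 0.90 = 0.09 twice and leaves out the intervention arm's 0.20 x 0.80 = 0.16.

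**4. Cluster size.** 4 x 97 = 388, not 412. If 412 is per arm, the cluster size is 412/4 = 103. If it is the total, the cluster size is 412/8 = 51.5. Neither is 97.

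**5. Power delivered.** Power = Phi(0.10 / sqrt(0.25 x VIF / n) - 1.96), with n per arm.

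| Reading | VIF | Effective n per arm | Power |
|---|---|---|---|
| 412 per arm, actual cluster size | 1 + 102 x 0.02 = 3.04 | 136 | 64% |
| 412 per arm, VIF as printed | 2.92 | 141 | 66% |
| 412 in total (206 per arm), actual cluster size | 1 + 50.5 x 0.02 = 2.01 | 102 | 53% |
| 412 in total (206 per arm), VIF as printed | 2.92 | 71 | 39% |

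**6. Detectable difference, 412 per arm.** Solve (p2 - 0.10) / sqrt((0.09 + p2(1 - p2)) x 3.04 / 412) = 2.80. The solution is p2 = 0.224, so the contrast is 10% versus 22.4%.

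**7. Ceiling with 4 clusters per arm.** As the cluster size grows, the effective size per arm tends to 4/0.02 = 200, which gives 81% power. Reaching 80% would need m = n(1 - 0.02) / (4 - 0.02n) children per cluster. That is about 2,500 for n = 196.2 and about 9,750 for n = 199. Taking 573 to 581 children per arm from the same four clusters raises the VIF to about 3.85 to 3.89 and gives only about 68 to 69%.

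**The case against.** The best defence is that 412 has an identifiable origin. It comes out almost exactly from the stated rates, power, significance level and inflation factor once a single variance is used for both arms. On that evidence 412 is per arm and already inflated. The shortfall in detectable effect is then modest: 22.4% instead of 20% in the intervention arm. The article calls 10 points a minimum, kits go only to the intervention arm, and the Background cites uptake of 8 to 88% elsewhere, so the true effect may be larger than planned. A confidence interval would also limit misreading of a null result.

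Much of this stands, and it narrows the point. It does not restore the 80%, which is claimed for 10 points and needs both arms' variances. A one-sided test would not rescue it either: 451 to 458 per arm would be needed, and 412 per arm gives about 75%.

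Three stronger readings are tempting but not supported:
- **The inflation factor was never applied.** Read as a total, 412 is 206 per arm, close to the unclustered 196 to 199. But the match at 412.5 per arm with the factor included is much closer.
- **The power delivered is about 50%.** That figure comes from a t reference with 6 degrees of freedom (8 clusters minus 2), a cluster-level test. Data management and analysis plans a mixed logistic model and does not name that test.
- **The intracluster correlation of 0.02 is too low.** The article gives no source for a higher value such as 0.05, and it gives shop counts only by arm (8 and 5), not by cluster.

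**Conclusion.** The point holds. The printed 80% power for the primary comparison does not follow from the printed inputs. They require 573 to 581 children per arm, and 412 is about 28 to 29% short of that if it is per arm (1 - 412/573 = 28%; 1 - 412/581 = 29%). Power for 10% versus 20% is then about 64 to 66%. On the less likely reading that 412 is the two-arm total, power is about 39 to 53%.

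These figures assume a two-sided 5% test, the normal approximation, equal cluster sizes and the article's own correlation of 0.02. The variance error and the per-arm meaning are inferences from the numerical match, because the article does not show its calculation. The shortfall does not depend on either inference, since no reading of 412 reaches 80%.

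A reader might infer that the survey should simply be enlarged. The documents do not support that as a practical remedy: four clusters per arm cap the effective size at 200, and the control arm has no further clusters to add.

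**What to change.** Rewrite the household-survey sample size paragraph:

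1. State whether 412 is per arm or the two-arm total, and whether the test is two-sided.
2. Correct the variance term to 0.10 x 0.90 + 0.20 x 0.80, and show the size before inflation.
3. Use the actual cluster size in the inflation factor: 103 gives 3.04 if 412 is per arm, and 51.5 gives 2.01 if it is the total.
4. Replace the 80% claim with what the design delivers. At 412 per arm this is about 64% power for 10% versus 20%, or 80% power for about 10% versus 22.4%. If 412 is the total, give about 53%.

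Small-sample figures may be added as sensitivity values labelled as assumptions. With a t reference on 6 degrees of freedom and 412 per arm, these are about 50% power for 10 points, or 80% power for 10% versus 25.3%. A higher intracluster correlation may be shown on the same terms.

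The cost is one paragraph. No children or clusters are added and the analysis does not change. The only downside is a less favourable stated power.

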### Inclusion criteria

The inclusion criteria based on the different data collection methods are as follows:

#### In-depth interviews

OTCMS within the selected clusters in both intervention and control arms

#### Baseline household survey

Children less than 10 years old in the intervention arm only

#### mRDT quality survey

Suspected uncomplicated malaria cases aged 6 months and above in the intervention arm only

#### End-line household survey

Children less than 10 years old in both intervention and control arms

### Exclusion criteria

The exclusion criteria based on the different data collection methods are as follows:

#### In-depth interviews

OTCMS outside the selected clusters

#### Baseline household survey

Children above 10 years old

#### mRDT quality survey

Children less than 6 months oldPregnant womenSigns and symptoms of severe malaria

#### End-line household survey

Children above 10 years old

### Safety considerations

Metallic waste bins will be provided to OTCMS in the intervention arm of the study for proper disposal of sharps used. RDT kits used will be harvested by the team for record purposes.

OTCMS will be trained on why clients with severe disease or those that are still feeling symptoms of illness but had been treated for malaria at the first visit should be referred to the nearest health center or the district hospital.

### Data management and analysis

The principal investigator (PI) will ensure that all implementation and evaluation activities are according to standard operating procedures. Quality assurance will include training of field workers/data collectors few days before data collection. The training will involve practical sessions. During data collection period, field supervisors will monitor study implementation through weekly visits to sites.

All data collected will be anonymized using only study numbers and stored in locked cabinets after entry into a computer with a password known only to investigators. Data will only be made available to authorized persons such as members of the institutional review board. Data will be double entered and verified using Microsoft Access 2010 (Microsoft Inc., Redmond, Washington) database, and later imported into STATA version 12.0 (STATA Corporation, College Station, Texas) for analysis. Any discrepancies will be corrected using source documents. To account for correlation within clusters, the generalized linear mixed model (GLMM) technique of analysis will be used in this study. Estimates from the logistic regression model with random effect will be used to determine the intervention effect. Data (recordings) collected during in-depth interviews will be transcribed, translated, and analyzed using NVivo 12 by QSR International. This will provide a better understanding of the quantitative observations.

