##### Acquisition of subsidized mRDT kits:

The research team will facilitate the acquisition of subsidized mRDT kits from the National Malaria Control Programme. The mRDTs will be provided to all OTCMSs in the selected intervention clusters only. mRDTs will be supplied on monthly basis to the various OTCMS participating in the study based on inventory. The OTCMS will be able to contact the research team anytime they are about to run out of stock. Stock management records will be kept by the research team to monitor the distribution of mRDTs. For the sake of identification purposes, the mRDTs will be stamped and OTCMS will be advised to store them in a cool, dry place. mRDT kits will be provided at no cost to participating OTCMS. They will be asked to price the mRDTs at a cost not more than the market wholesale price of GH¢2.40/kit (~$0.44).

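### With 4 clusters per arm, the random-effects logistic model needs a small-sample test: its default large-sample Wald test has a type I error of about 10 to 12%, not 5%

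*Protocol article*

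**What the plan says.** All statements are in the Protocol article.

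- **Model (Data management and analysis).** To allow for correlation within clusters, "the generalized linear mixed model (GLMM) technique of analysis will be used in this study", and "Estimates from the logistic regression model with random effect will be used to determine the intervention effect". The article gives no test statistic, reference distribution or degrees of freedom.
- **Clusters (Study design).** The trial is a "cluster randomized trial across 8 rural clusters (4 clusters per arm), in two adjacent districts of Ghana".
- **Sample size (Sample size estimation, Household survey).** The target is 20% testing against 10%, "with 80% power and 5% significance level". The variance inflation factor of 2.92 is "based on an intracluster coefficient of 0.02 and an average cluster size of 97". The count reads: "A total of 412 children under 10 years of age in 4 clusters per arm will be sampled". This can mean 412 per arm (103 per cluster) or 412 in all (51.5 per cluster).
- **Denominator (Primary outcome).** Children under 10 with fever or suspected malaria who visited an over-the-counter medicine seller.
- **Kit supply (Acquisition of subsidized mRDT kits).** "The mRDTs will be provided to all OTCMSs in the selected intervention clusters only".

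**The concern.** The intervention is applied to whole communities, so the uncertainty in its effect comes mainly from how much communities differ. That spread has to be estimated from 8 clusters. Two things then go wrong with ordinary large-sample output from a random-effects logistic model. Maximum likelihood tends to underestimate the between-cluster variance, and the Wald z treats that estimate as if it were known. Both make intervals too short and p-values too small.

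The primary outcome rests on this test, and the Discussion says a positive result will be used for advocacy by the national malaria programme. A false-positive risk near one in ten, reported as one in twenty, matters for that use.

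**Working it through.** **1. The plan's own figures.** The inflation factor reproduces: 1 + (97 − 1) × 0.02 = 2.92. The count of 412 does not follow from 10% versus 20%: the usual two-proportion formula gives 199 per arm, and 199 × 2.92 = 581.1, so 582 per arm. That is a separate matter. Here 412 serves only to set the cluster size, and both readings are carried forward.

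**2. Check by hand.** Between-cluster df = 8 − 2 = 6. The two-sided 5% critical value is 1.960 for the normal and 2.447 for t on 6 df. The 10% point of t on 6 df is 1.943. A statistic that truly follows t on 6 df but is judged against 1.960 therefore rejects just under 10% of the time, before any downward bias in the variance. Normal-based intervals are also too short: 2.447 / 1.960 = 1.25, so the correct ones are about 25% wider for the same standard error.

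**3. Simulation under no effect.** Inputs: 4 + 4 clusters, beta-binomial outcomes, 10% testing in both arms, nominal two-sided 5% (the article does not state sidedness). The random-intercept logistic model was fitted by maximum likelihood. Rejection rates:

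| Children per cluster | ICC | Logistic, Wald z | Logistic, t on 6 df | Cluster proportions, t on 6 df |
|---|---|---|---|---|
| 103 | 0.02 | 11.3 to 12.2% | about 6 to 6.5% | 4.5 to 5.0% |
| 97 | 0.02 | 12.2% | 5.7% | 4.6% |
| 52 | 0.02 | 9.1 to 9.9% | about 4% | 4.7 to 5.0% |
| 103 | 0.05 | 13.1% | 6.9% | 4.0% |
| 103 | 0.10 | 13.1% | 6.6% | 4.2% |
| 20 | 0.02 | 5.8% | 1.0% | 5.2% |

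Ranges come from separate implementations with 2,000 to about 5,000 runs each. The likelihood ratio test does not cure the problem: it gave 8 to 10% at ICC 0.02 with 52 to 103 per cluster. At ICC 0.05 the Wald result depends on numerical integration: 25 fixed quadrature points gave 18%, and 101 points gave 13.1%. A refit on a fine grid agreed with 13%, so 18% is treated as a numerical artefact.

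**4. Power for 10% versus 20%, cluster-level t-test, ICC 0.02.** The variance of the difference is [0.10 × 0.90 + 0.20 × 0.80] × [1 + (m − 1) × 0.02] / (4m).

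- m = 103: 0.25 × 3.04 / 412 = 0.001845, SE 0.0430, noncentrality 0.10 / 0.0430 = 2.33, power on 6 df 49.8% (simulated 50.5%).
- m = 51.5: 0.25 × 2.01 / 206 = 0.002439, SE 0.0494, noncentrality 2.02, power 39.9%.

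At m = 103 the simulated power was about 74% for the uncorrected Wald z and about 60% for the same model on t with 6 df. The difference between 74% and 60% comes only from using too small a critical value.

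**5. No tested child in the control arm.** The logistic model then has no finite effect estimate. Take 0/52 in each control cluster and 8, 12, 10 and 14 of 52 in the intervention clusters. As the log odds ratio is moved through 4.7, 8.7 and 16.7, the likelihood keeps rising while the Wald z falls through 3.3, 0.84 and 0.03. The cluster-level test stays defined at t = 8.5. All the variance now comes from four clusters, so the right df is 3, not 6: simulated coverage of the 95% interval was about 90.5% on 6 df and about 94.5% on 3 df. An unequal-variance df gives 3 automatically here.

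**The case against.** **The Wald test is not in the text.** A reader might infer that the protocol prescribes a faulty test. It does not. It names a model, a condensed article may leave the reference distribution to an analysis plan that is not shown, and the same model on t with 6 df is close to nominal at the planning inputs. This stands as a limit on the wording. It does not dispose of the point: the article fixes this model with 8 clusters, and its ordinary large-sample tests, Wald or likelihood ratio, miss the stated 5%.

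**The size depends on the analysed number.** Only children who were ill and visited a seller count, so the number per cluster may fall well below 103. This stands: at 20 per cluster the inflation is gone. At that size, however, the logistic model on t with 6 df becomes very conservative (1.0%), while the cluster-level test stays at about 5%.

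**The analysis will fail because control shops receive no kits.** A reader might infer this from the kit supply. The documents do not support it. The sample size assumes 10% testing in control, and also 10% in the intervention arm before any study kits arrive. At 10% and ICC 0.02, the chance of no tested control child is below 0.000001 at 52 or 103 per cluster and 0.0008 at 20. It matters only if the true rate is far lower: at an assumed 1% it is 11%, 23% and 50% for 103, 52 and 20 per cluster.

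**The odds ratio is on the wrong scale.** Sizing on proportions and analysing by logistic regression is routine, and a risk difference can be derived from the model. This is not a fault.

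**A permutation test would be an exact check.** Study design describes arms set by area: 4 of 8 clusters are drawn at random within the intervention area, and all 4 control clusters are taken. The relabellings of 8 clusters are therefore not the design's set of possible assignments, and the test would not be exact.

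**Conclusion.** The point holds. If the stated model is run with its default Wald test on 4 clusters per arm, the type I error is about 10% (52 per cluster) to 12% (about 100 per cluster) instead of 5%, at 10% testing and ICC 0.02. It reaches about 13% at ICC 0.05 and is near nominal at about 20 eligible children per cluster.

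This rests on a two-sided 5% level, equal cluster sizes, beta-binomial variation, and a large-sample test being used because none is named. The breakdown with an empty control arm is a conditional caution: possible, but not expected under the assumed 10%. It is a further reason to prefer the cluster-level analysis, not a separate failure of the plan.

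**What to change.** In Data management and analysis, before end-line data are analysed:

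1. Make the primary analysis a comparison of the 8 cluster testing proportions: difference in means, t-test and 95% confidence interval on 6 df. State that an unequal-variance df is used if one arm shows no variation between clusters.
2. Keep the random-effects logistic model as secondary, with its Wald statistic referred to t on 6 df and enough integration points for the fit to be stable.
3. Do not add a permutation test as an exact check.

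The cost is wording only, with no change to data collection. Intervals become wider. Power for 10% versus 20% at ICC 0.02 and 103 per cluster is about 50% (about 60% for the logistic model on t with 6 df) instead of an inflated 74%, and about 40% if 412 is the total. That is what 8 clusters support, and the investigators should know it before the analysis.
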